## Abstract

**Background:**

Children in foster care are psychologically vulnerable and show more social, developmental, and behavioral problems than those living with their family of origin. Many foster parents struggle to care for these children, some of whom have experienced severe adversity. Research and theory suggest that developing a strong and supportive foster parent–child relationship is essential for foster children to become more well-adjusted and experience a decrease in behavioral problems and emotional maladjustment. Mentalization-based therapy (MBT) for foster families aims at increasing the reflective functioning of the foster parents, thus promoting the development of more secure and less disorganized child attachment representations, which is subsequently proposed as a factor that reduces behavioral problems and emotional maladjustment in children and promotes their overall well-being.

**Methods:**

This is a prospective cluster-randomized controlled trial with two conditions: (1) the intervention group participating in MBT, and (2) the control group who receive usual care. Participants are 175 foster families with at least one foster child aged 4–17 years with emotional or behavioral problems. The intervention will be offered to foster families by 46 foster care consultants from 10 municipalities in Denmark. The foster care consultants will be randomized to MBT training (n = 23) or usual care (n = 23). The primary outcome is the psychosocial adjustment of the foster child measured by the Child Behavior Checklist (CBCL) as reported by foster parents. Secondary outcomes include child well-being, parental stress, parent mental health, parent reflective function and mind-mindedness, parent/child relations, child attachment representations, and placement breakdown. In order to explore implementation fidelity as well as practitioner experiences, we will administer questionnaires designed for this study and conduct qualitative research exploring the practice of the MBT therapists.

**Discussion:**

This trial is the first experimental study of a family therapeutic intervention based on attachment theory for foster families within the Scandinavian context. This project will contribute with novel knowledge on attachment representations in foster children and the effects of an attachment-based intervention on essential outcomes for foster families and children.

*Trial registration* ClinicalTrials.gov NCT05196724. Registered on January 19, 2022.

## Background

Children in foster care are psychologically vulnerable and show more social, developmental, and behavioral problems than children who live with their family of origin [1, 2]. Many foster children have experienced adverse events before their initial placement, such as physical and emotional abuse and neglect [3]. Furthermore, studies show that children in out-of-home care face significantly higher risks of mental health problems [4, 5], drug and alcohol abuse [6], and suicidal behavior [4, 7, 8] when compared to the general population. Removing a child from their family of origin and placing them in foster care can be a traumatic event for the child and, in some cases, does not improve a child’s life-course [9]. Research is equivocal about the long-term effects of foster care, with studies finding both negative and positive effects on foster children’s developmental trajectories, as measured by behavioral, emotional, and mental health outcomes [9–11].

While a secure, long-term placement is associated with better long-term outcomes for children in foster care [12, 13], placement breakdown is relatively common. Placement breakdown can have devastating consequences for vulnerable children and is costly for society [9, 14]. In Denmark, around 8% of children in foster care experience placement breakdown [15], which typically occurs when foster parents feel unable to care for the child [16]. Many foster parents struggle to manage the complex care needs of the children placed in their care [17]. Therefore, understanding and supporting the needs of foster families is essential if we are to improve the long-term outcomes of children in foster care.

### Attachment representations of children placed in foster care

Theoretically, the difficulties experienced by foster families and the behavioral and emotional symptoms exhibited by the children may be understood through an attachment lens [18]. According to attachment theory, early caregiving experiences influence adaptation and maladaptation across the lifespan by organizing the child’s individual and relational developmental processes “from the cradle to the grave” [19]. Through interactions with the primary caregiver and based on the caregiver’s responses to the child, internal working models of attachment are established early in life. A child will experience grief, anger, and distress as a result of loss of access to existing attachment figures, and this can only be resolved if the child can develop new attachment relationships with alternative caregivers [20]. The child’s attachment pattern can be categorized as either secure or insecure [21], and a secure attachment relationship with a primary caregiver has long-term benefits for children [22]. Some children who experience early trauma, such as harsh neglect and abuse or the loss of their biological parents, may develop disorganized attachment representations, which leaves the children without stable internal working models of intimate relationships. Children who experience abuse and neglect are also at an increased risk of developing reactive attachment disorder (RAD) or disinhibited social engagement disorder (DSED) [23]. Although clinically distinct from each other, the two disorders share common features, and both represent disorders of attachment rooted in early traumatic experiences, which are common among children placed in foster care [23].

Research into child attachment representations and attachment classification of children in foster care is surprisingly scarce. In a meta-analysis of international research, Vasileva and Petermann [24] only identified five studies reporting on child attachment style for children in foster care (n = 255). Only one study was from Europe (the Netherlands), whereas the remaining four were from the US. Based on the meta-analysis, it was estimated that disorganized attachment occurs in 22% of children in foster care and that 43% of children in foster care have an insecure attachment style [24].

Hillman, Cross, and Anderson [25] measured attachment representations by using a story stem approach in which attachment narratives are coded in a dimensional manner. The study compared data from a sample of children placed in foster care with a matched sample of non-maltreated children who lived with their biological parents. The study concludes that the children in the foster care sample consistently displayed more disorganized, avoidant, and negative representations and had significantly fewer representations characteristic of secure attachment [25].

Despite the insights provided by the above studies, there remains a scarcity of research into the attachment representations of children placed in foster care; in a Scandinavian context, until the contribution of the present study, there had been no studies of the attachment representations of children placed in foster care.

### Theory of change in attachment-based interventions

Disorganized attachment representations are highly predictive of later socioemotional maladjustment and behavior problems in children, and similarly, more secure attachment representations are a protective factor for long-term child outcomes [26]. Attachment is a relational and dynamic phenomenon. When a traumatized child is placed in the care of sensitive caregivers who can consistently empathize with the child and understand that the child’s destructive or negative behavior may result from the child's negative prior experiences of abuse and neglect, the child may develop more secure and less disorganized attachment representations [22]. Development of more secure attachment and less disorganized child attachment representations are proposed as factors that can reduce behavioral problems and socioemotional maladjustment symptoms in the children. Understanding and promoting the mechanisms by which foster parents can help children placed in their care to develop more secure and less disorganized attachments is, therefore, an urgent priority [18].

Based on the original conception by Mary Ainsworth, parental sensitivity is defined as a parent’s ability to (1) notice child signals, (2) interpret these signals correctly, and (3) respond to these signals promptly and appropriately [27, 28]. The quality of the attachment bond between child and parent is highly dependent on the sensitivity of the caregiver [22, 29–31]. A growing evidence base indicates that increased parental reflective functioning (PRF) combined with parental sensitivity lead to positive child outcomes [32–34]. Parental reflective functioning refers to the parental ability to hold the child’s mind in mind and understand the child’s behavior as a result of inner thoughts and feelings that may result from early negative experiences [32, 35]. The central mechanism of change in attachment-based interventions is to support the foster parents in meeting the child's needs [36]. This can be done by helping the foster parents to understand the subtle and overt emotional cues in the child's behavior and to respond to these cues in a sensitive and contingent manner.

Reviews of attachment-based interventions for at-risk families with young children find positive effects on parental sensitivity and infant attachment [37, 38]. Reviews examining the effects of attachment-based interventions offered to foster parents and adoptive parents find similar promising results. A narrative review of attachment interventions for foster and adoptive parents and children aged 0–17 years suggests positive effects but also points to the need for larger and more methodologically sound randomized controlled trials of attachment-based interventions that have proven efficacy in biological parent–child dyads [39]. A meta‐analytic review examining the effects of all types of parenting interventions in foster care and adoption finds strong positive effects on sensitive parenting and positive results on dysfunctional discipline, parenting knowledge and attitudes, parenting stress, and child behavior problems. The authors point out that future studies should focus solely on either foster care or adoption populations [40]. Finally, a recent systematic Campbell review explored the effects of attachment-based parenting interventions for foster and adoptive families. The review included 44 studies reporting 27 different samples (19 randomized trials and eight non-randomized studies) [18]. The meta-analyses show improvement in the overall psychosocial adjustment of the child and improvement of positive parent and child behavior and parenting stress post-intervention. Results also show improvement in observed positive parenting behavior 3–6 months after the interventions. Within the review, a meta-analysis was conducted using attachment outcomes. However, in line with the findings regarding the prevalence of attachment representations and attachment styles in foster children, the meta-analysis using attachment as an outcome was inconclusive due to the very limited number of studies that reported on attachment as an outcome (k = 3) [18].

The existing reviews thus show promising results for attachment-based interventions used with foster families. However, there is a need for high-quality RCTs, especially on interventions that target the underlying mechanisms in promoting more secure and less disorganized attachment representations in foster children.

### The intervention: mentalization-based therapy (MBT) for foster families

Most attachment-based parenting interventions are designed for relatively young children [17]. This is reflected in the fact that the mean age of the children included in a recent review of attachment-based interventions was 5.15 years [18]. In Denmark, however, children who are placed in foster care are 11.3 years on average at their first placement [44], and thus there is a strong need for interventions to support foster families with older children. Compared to other attachment-based interventions, MBT can be used with a much broader age range of children. The MBT approach is relatively new to psychological therapy and grew out of developments in psychodynamic therapy and attachment research [41, 42]. Mentalization-based therapy is a short-term semi-manualized treatment. Programs using MBT have been used on many different populations, including parents and babies, adolescents who self-harm, and adults with borderline personality disorder [43–46]. Studies have demonstrated that when parents or foster parents are more sensitive and better able to 'mentalize' their child, these abilities are associated with a range of improved outcomes for children. When used in the context of foster care, MBT aims to promote the quality of relationships, support effective and sensitive foster care, and support foster parents in helping the child understand and manage emotions better. The focus is on improving the core components of secure attachment, particularly by developing reflective functioning for all professionals working with children in out-of-home care. This reflective functioning is assumed to increase the child's psychosocial adjustment and decrease emotional and behavioral problems [33].

Mentalization-based therapy programs consist of up to 12 weekly sessions with the foster parents and child or children covering three core components: (1) psycho-education about mentalizing, trauma, and attachment for foster parents; (2) support for reflective practice in the professional network; and (3) mentalization-based therapy for the foster family [36]. Mentalization-based therapy is a flexible intervention in which therapists can adjust the content and activities within each session to fit the needs of the foster family [36]. Within MBT sessions, the therapists may work with the foster child and parents together or separately. Mentalization-based therapy sessions consist of either therapeutic conversations or activities in which the therapist uses a playful and genuinely curious approach to encourage mentalizing in the foster parents and the child or children. Similarly, the therapists work to prevent breakdowns in mentalizing, which are often caused when families are under stress, by providing a positive example and actively intervening when non-mentalizing dialogue and interactions occur. Therapeutic activities include games, artwork, and role-plays adjusted to fit the child's age, development, and interests [41].

A randomized feasibility study of MBT for foster families in the UK with 36 families found positive results regarding implementation, training of therapists, and acceptance from foster parents. However, it was not possible to estimate a reliable effect size due to the relatively small sample size [41]. The single outcome measure used showed divergent results. Children in the MBT condition reported a large, significant improvement in internalizing symptoms compared to usual care (UC). In contrast, foster parents reported an insignificant improvement in internalizing symptoms favoring the UC group [41]. The study concludes that while the feasibility of the trial had been established, “A full-scale definitive trial with follow-up at the end of all treatments is needed to determine efficacy” [41]. The present trial will be the first experimental study of an attachment-based family therapeutic intervention for foster families and children within the Scandinavian context.

### Research aim

For foster families with children aged 4–17 years, this study examines the effects of MBT, compared to usual care, on child psychosocial adjustment and well-being, parental stress, mental health, reflective function, parental mind-mindedness, and the foster parent–child relationship. The primary outcome is child psychosocial adjustment as measured by the Child Behavior Checklist (CBCL) reported by foster parents and self-report for children aged ten or above. A secondary aim of the study is to provide knowledge about attachment representations in foster children aged 4–11 and how these may be associated with the child's psychosocial adjustment.

We hypothesize that MBT is superior to UC on measures of child mental health and well-being, parent stress, parent–child relationship, foster parent reflective functioning, parental mind-mindedness, and placement stability. We also hypothesize that a high proportion of young foster children will show signs of disorganized and insecure attachment representations that will be associated with psychosocial maladjustment.

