### Primary outcome

The Child Behavior Checklist (CBCL) measures psychosocial adjustment and is a component of the Achenbach System of Empirically Based Assessment (ASEBA) [51, 52]. The ASEBA is used to detect behavioral and emotional problems in children and adolescents. The CBCL consists of 113 questions, scored on a three-point Likert scale (0 = absent, 1 = occurs sometimes, 2 = occurs often). Foster parents for all children in the trial will complete the CBCL. The CBCL/6–18 (used with children 6 to 18 years old) consists of eight syndrome scales: (1) anxious/depressed, (2) depressed, (3) somatic complaints, (4) social problems, (5) thought problems, (6) attention problems, (7) rule-breaking behavior, and (8) aggressive behavior. The syndrome scales group into two higher-order factors: (1) internalizing and (2) externalizing. The timeframe for item responses is the past six months. The CBCL also includes competence scales for activities, social relations, school, and total competence. The CBCL is widely used and has proven to be a useful tool for detecting psychopathology in children and shows good results regarding both validity and reliability [53]. Danish norms are available for children throughout the age range of children within the trial [51, 52]. A low score on the Total Problem Scale is beneficial.

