### Secondary outcomes

Kidscreen-10 is a ten-item parental and self-report measure of child well-being (health-related quality of health) [54]. Items are scored from 1 (never) to 5 (always) except for items 1 and 9 (reverse). Items 1 and 2 explore the level of the child’s/adolescent’s physical activity, energy, and fitness. Items 3 and 4 cover how much the child/adolescent experiences depressive moods and emotions, and stressful feelings. Items 5 and 6 ask about the child’s/adolescent’s opportunities to structure and enjoy their social and leisure time and participation in social activities. Item 7 explores the quality of the interaction between the child/adolescent and parent or caregiver and the child’s/adolescent’s feelings toward their parents/caregivers. Item 8 examines the nature of the child’s/adolescent’s relationships with other children/adolescents. Finally, items 9 and 10 explore the child’s/adolescent’s perception of their cognitive capacity and satisfaction with school performance. A higher score is better [54]. Kidscreen-10 is used as a self-report measure for children aged 10 or above, while the parental rating version is used within all families.

The Strengths and Difficulties Questionnaire (SDQ) [55, 56] for 11–17-year-old children is a 25-item measure of child behavior and psychopathology. Items are rated by the foster child on a three-point scale (not true, somewhat true, certainly true). The SDQ consists of five domains: hyperactivity/inattention, peer problems, conduct problems, emotional symptoms, and pro-social behaviors. The SDQ also has an additional seven-item impact supplement about daily function. Foster children from 10–17 years old will receive the SDQ. A high score indicates more problems.

The Parental Reflective Functioning Questionnaire (PRFQ) is an 18-item measure of parental reflective function or mentalization [57]. The PRFQ consists of three subscales. The first subscale: Pre-Mentalizing Modes (PRFQ-PM) contains 6 items (a low score indicates better function). The second subscale: Certainty about Mental States (PRFQ-CMS) contains 6 items (a high score indicate better function), and the third subscale: Interest and curiosity in mental states (PRFQ-IC) also contains 6 items (a high score indicate better function) [57]).

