### Statistical analysis

We will estimate the mean treatment effect of MBT relative to UC on the primary outcome (CBCL) as well as each of the secondary outcomes (Parental Well-Being, Stress, and Reflective Functioning, SDQ, Kidscreen, SSAP, and Parental Mind-Mindedness) at T2 and T3 separately, but using the same method each time, as follows.

Treatment assignment will be stratified into municipalities, and within each stratum, it will be assigned to clusters based on foster care consultants. Hence the estimation needs to account for both the stratification and the clustering. We will thus use linear regression for T2 and T3 outcomes separately, in each case controlling for pre-treatment outcomes. Within each stratum, we will then use linear regression, estimating robust clustering standard errors in order to account for the potential correlation between subjects assigned to the same consultant. Using the strata-specific treatment effects, we will then compute the mean treatment effect as the weighted mean of the within-stratum estimates weighted by stratum share. We can calculate the variance by averaging the within-stratum cluster robust variance, weighted by stratum share squared [70]. All analyses will use a significance level of 0.05.

Analyses will be based on the intention-to-treat (ITT) principle, analyzing each subject as part of the treatment to which they were originally assigned, regardless of whether treatment was in fact received.

If there is substantial attrition in outcome data collection, this will potentially introduce selection bias in the estimated effect if attrition selection is on unobservables. While doing so does not solve the problem of attrition selection on unobservables, we will follow the standard in the literature and analyze sensitivity by handling missing values using multiple imputation using all baseline variables.

Further, we will perform subgroup analysis in order to examine whether treatment effects differ across subgroups based on age (4–9 and10–17 years), number of previous foster care placements, municipality budget per capita (low or high) as well as parental background variables.

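### The primary outcome is tested at T2 and at T3, each at an unadjusted 0.05, with neither wave ranked, and the Research aim adds a self-report that the other sections treat as secondary

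*Protocol article*

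**What the plan says.** **Waves and significance level.** The Statistical analysis section gives one method for the effect of MBT "on the primary outcome (CBCL) as well as each of the secondary outcomes" and applies it "at T2 and T3 separately, but using the same method each time, as follows". It then states: "All analyses will use a significance level of 0.05". T2 is 20 weeks after baseline and T3 is six months after T2 (Outcomes). Neither is called primary anywhere in the article.

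**Sample size.** Power considerations assumes d = 0.53, power 0.80, type 1 error 0.05, ICC 0.1 and 23 consultants per arm. It arrives at 3 families per consultant, 138 in all, with a recruitment target of 175.

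**Informant.** The abstract states: "The primary outcome is the psychosocial adjustment of the foster child measured by the Child Behavior Checklist (CBCL) as reported by foster parents". The Primary outcome section agrees: "Foster parents for all children in the trial will complete the CBCL". The Research aim differs and defines the primary outcome "as measured by the Child Behavior Checklist (CBCL) reported by foster parents and self-report for children aged ten or above". The self-report of psychosocial adjustment in Table 1 is the SDQ, which is described under Secondary outcomes ("Foster children from 10–17 years old will receive the SDQ") and is listed among the secondary outcomes in Statistical analysis.

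**Score.** The Primary outcome section describes syndrome scales, internalizing and externalizing factors and competence scales. It gives the favourable direction of the Total Problem Scale but does not say that this scale is the primary score.

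**The concern.** A primary outcome should lead to one decision at the stated error rate, or to several decisions under a stated rule. Here two tests of the primary outcome each receive the full 0.05, and the article does not say what follows if one wave is significant and the other is not. A reader of the results could not tell which of them answers the primary question, and the authors could in good faith lead with either. This is more than a detail left to an analysis plan, because the article itself fixes separate tests and applies 0.05 to all of them.

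The Research aim adds a second uncertainty, about who reports the outcome. The choice can matter: in the earlier UK feasibility study of 36 families described in the background, children reported a significant improvement in internalizing symptoms with MBT, while foster parents' reports leaned non-significantly towards usual care. That study was small, and the article says it could not give a reliable effect size, so it only illustrates that informants can differ.

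**Working it through.** **1. The plan's own sample size (Power considerations).** Two-sided testing is assumed, since the article does not state it.

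- Families per arm without clustering: 2 × ((1.960 + 0.842) / 0.53)² = 55.9, so 56.
- Design effect at 3 families per consultant: 1 + (3 − 1) × 0.1 = 1.2.
- Families per arm with clustering: 56 × 1.2 = 67.2. Per consultant: 67.2 / 23 = 2.92, rounded up to 3.
- Total: 3 × 46 = 138. The stated figure is reproduced.
- Power at 138: effective size per arm 69 / 1.2 = 57.5; 0.53 × √(57.5 / 2) = 2.842; Φ(2.842 − 1.960) = 0.81 (0.79 with a t distribution on 44 df).

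So the calculation is right for one test at 0.05.

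**2. False-positive chance with two waves, each at 0.05 two-sided.** Under no effect at either wave, let Z₂ and Z₃ be standard normal with correlation ρ. The article gives no ρ, so a range is shown. The success rule assumed is significance at either wave.

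- Either direction: P(|Z₂| > 1.96 or |Z₃| > 1.96). For ρ = 0 this is 1 − 0.95² = 0.0975.
- Favouring MBT only: P(Z₂ > 1.96 or Z₃ > 1.96), with the sign taken so that positive favours MBT. For ρ = 0 this is 1 − 0.975² = 0.0494.
- For ρ > 0 both come from the bivariate normal distribution.

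| ρ between the waves' tests | Either direction | Favouring MBT |
|---|---|---|
| 0 | 9.75% | 4.9% |
| 0.5 | 9.1% | 4.5% |
| 0.8 | 7.8% | 3.9% |
| One test only | 5.0% | 2.5% |

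**3. Power if both waves stay primary at 0.025 each** (critical value 2.241).

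- 138 families: Φ(2.842 − 2.241) = 0.73 (t, 44 df: 0.70).
- 175 families, no drop-out: 175 / 46 = 3.80 per consultant; design effect 1 + 2.80 × 0.1 = 1.28; effective size per arm 87.5 / 1.28 = 68.3; 0.53 × √(68.3 / 2) = 3.098; Φ(3.098 − 2.241) = 0.80 (t: 0.78).
- For 0.80 at 0.025: families per arm without clustering 2 × ((2.241 + 0.842) / 0.53)² = 67.7; solving m = 67.7 × (1 + (m − 1) × 0.1) / 23 gives m = 3.75, or about 173 families.

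**4. Informant, section by section.**

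| Section | Primary outcome |
|---|---|
| Abstract, Methods | Foster-parent CBCL |
| Research aim | Foster-parent CBCL and self-report from age 10 |
| Primary outcome | CBCL, completed by foster parents |
| Secondary outcomes | Self-report SDQ placed here |
| Statistical analysis | CBCL primary, SDQ secondary |

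Only the Research aim departs from the rest. No self-report version of the CBCL appears in Table 1, so the added phrase could refer only to the SDQ.

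**The case against.** The strongest reply is that the article plans an estimate at each wave and never says that success at either is enough. That is fair, and the error rates above depend on that assumed rule. But the article gives no other rule, and significance at 0.05 is declared for both waves. A second reply is that the two-sided figures count false positives favouring usual care, whereas this is a superiority trial. That also stands: the rate of false claims for MBT is about half the two-sided figure, though still well above 2.5%. Third, an analysis plan that is not shown may name the wave. It may, but it would then have to override what the article states.

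Four stronger readings are tempting and are not supported.

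- **Four primary tests (two informants by two waves).** This needs the Research aim to override every other section. The weight of the text makes the SDQ secondary, so the phrase is best read as a drafting slip, and no four-test error rate should be attributed to the plan.
- **A wrong power calculation.** Power at each wave is as stated. It falls only if alpha is divided.
- **No common score for children aged 4–5.** The article says "The CBCL/6–18 (used with children 6 to 18 years old) consists of eight syndrome scales", but it also says that foster parents of all children complete the CBCL and that Danish norms cover the trial's age range. This leaves room for another form at younger ages that a condensed article does not describe.
- **T3 as the correct primary wave.** The article does not settle this. T2 is the post-intervention assessment, and the Discussion expects attrition in the control group to be a problem.

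**Conclusion.** The concern holds for the two waves. As written, the primary outcome is tested twice at full alpha in a trial sized for one test. If significance at either wave counts as success, with two-sided tests and correlations of 0.5 to 0.8 between them, the chance of a false-positive primary result is about 7.8–9.1% instead of 5% (9.75% if the tests were independent). For false claims in favour of MBT it is about 3.9–4.5% instead of 2.5%. The firm count is two tests. The rule, the sidedness and the correlations are assumptions.

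The self-report phrase in the Research aim is a plain contradiction with the other sections. On its own it is a minor correction, but it should go in the same revision because it bears on what the primary outcome is. The sample size of 138 stands once a single primary test is named.

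**What to change.** 1. In the Research aim, delete the words that add self-report for children aged ten or above.
2. State foster-parent CBCL Total Problems as the primary score wherever the primary outcome is defined.
3. Name one wave, T2 or T3, as primary and test it at 0.05. The choice is the sponsor's and must be fixed before any unblinded analysis. Make the other wave and the SDQ self-report secondary.

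This is a change of wording. It needs no new data and leaves the 138-family calculation intact. The cost is that one wave gives up its claim to the primary conclusion.

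If both waves are to stay primary, state a rule: Holm, or a fixed sequence with the order given. With 0.025 per test, restate the power as about 0.73 at 138 families and about 0.80 at 175 with no drop-out. About 173 families would then be needed for 0.80, which uses nearly all of the margin that Power considerations sets aside for drop-out and moderator analyses. Under a fixed sequence the first wave keeps 0.05 and its stated power, and the second is tested only if the first succeeds.
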